### Translational studies

Multiplex IHC will be performed on all archival samples for determination of; (i) CD3+, CD8+TILs, CD8+/CD4+FOXP3+TIL ratio, CD137+CD8+TILs, CD137+CD8+/CD4+FOXP3+TIL ratio, peritumoral lymphocytes and correlation with response; (ii) expression of immune checkpoints including TIM-3, LAG-3, CTLA-4, PD-L2, PD-L1, PD-1, and correlation with response; (iii) targeted next generation T-cell receptor sequencing (Adaptive biotechnologies) to determine T-cell clonality and correlate with response. Multiparameter flow cytometry will be used to determine the effect of treatment on circulating CD8+, CD4+FOXP3+T-cells. Cytokine analysis will also be performed to measure IFN-α, IFN-β, TNF-α, IL-6, IL-10, IL-12, and IL-2 levels and correlated with response. This will allow for comprehensive baseline profiling that will be correlated with treatment response. This approach has been validated as a means to determine the potential predictive value of immune cell phenotype and spatial distribution relative to the tumor [28]. This might allow for a better understanding of patients who might benefit from this form of combined therapy. We will collect HPV status, and MSI status at baseline. Identification of microsatellite instability resulting from defects in the mismatch repair pathway and specifically within MLH1, MSH2, MSH6 and PMS2 have been suggested to portend a significantly improved response to checkpoint blockade [29]. This information will be correlated with treatment response. One of the key mechanisms via which cisplatin-sensitized radiation therapy mediates its immunogenic effect is via calreticulin exposure, release of ATP, induction of programmed death receptor 1-ligand (PD-L1) and high-mobility protein box-1 (HMGB-1) [20, 21]. As such, we will measure baseline serum HMGB1 and at cycle 1, day 1 (D1), D5, D8, D12, D15, D19, D22 and D26 while on combination therapy via commercially available ELISA assays.

### Statistical considerations

The target enrolment is 24 patients. The primary endpoint for this study is overall response rate (ORR). This sample size calculation is based on an ORR of ≥ 60%. For recurrent metastatic disease, there are is no standard of care. The ORR estimation is informed by data showing an ORR of 40% in patients with advanced or recurrent metastatic vulvar cancer treated with platinum-based combination therapy [4]. Single-agent chemotherapy has an ORR of about 12% [5]. Patients with primary disease who are not candidates for upfront surgery have a reported response rates from 55% [30] to 64% [11]. Only patients who undergo treatment on protocol will be eligible for analysis. Patients who sign consent and do not undergo any treatment will be ineligible for evaluation. With n = 24, the power to reject Ho: ORR ≤ 30% in favor of H1: ORR ≥ 60% will be 89% at a target significance level of 0.05 for a one-sided exact Binomial test (12 or more responses are required to reject Ho in favor of H1). Six-month Recurrence Free Survival (RFS-6) is the secondary endpoint. Exploratory biomarkers include; Predictive values of baseline dMMR/MSI-status and PD-L1; Anti-tumor inflammatory responses of cGas-STING- pathway, systemic inflammatory cytokines, and circulating T-cell receptor repertoire.

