For patients with regional lymph node metastasis, extra nodal extension of the tumor, or fixed/ulcerated nodal metastasis (FIGO III/IVA), upfront surgical debulking results in significant morbidity and mortality [7, 8]. Single-agent platinum therapy is inefficacious for this disease, as illustrated by the absence of any clinical responses to cisplatin monotherapy [9]. Chemoradiation has been shown to offer significant improvements in response rate, relapse-free survival and overall survival over RT in patients with locally advanced disease [10]. As such, upfront chemoradiation has been the generally employed standard. GOG 205 evaluated the clinical response rates in patients with locally advanced squamous cell vulvar carcinoma treated with cisplatin-sensitized radiation therapy [11]. They reported a 64% response rate, allowing for many of these patients to subsequently undergo consolidative surgery. The addition of consolidative surgery after chemoradiation does not confer any significant increase in overall survival over chemoradiation alone [12]. Although the addition of chemotherapy to radiation has been shown to improve survival time to up to 44 months in patients with node-positive disease [13], there is room to increase recurrence free survival in this patient population.

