## Methods

### Aim and study design

The purpose of this study is to capitalize on the immunogenic properties of concurrent cisplatin/radiation via addition of pembrolizumab. Addition of pembrolizumab to cisplatin-sensitized radiation (Cis-RT) therapy is hypothesized to increase overall response rate, and recurrence free survival via increased cytotoxic T-cell engagement and activation. Based on this hypothesis, immunotherapy would need to be given concurrently with Cis-RT. Unlike CTLA-4 inhibitors, pembrolizumab has not been shown to have a dose-dependent relationship to toxicity with the currently utilized dose of 200 mg/m^2^ every 3 weeks. Due to this, a phase 1 trial with varying doses of pembrolizumab would not be instructive regarding toxicity and would likely impact potential efficacy. Also, due to the long half-life and frequency of administration, to test the hypothesis of synergy outlined in this study, pembrolizumab has to be present when Cis-RT is given. This makes a phase 2 trial design with pembrolizumab lead-in less ideal. In light of this, we decided to pursue a single-arm phase 2 clinical trial of concurrent Cis-RT and pembrolizumab. Finally, published and emerging toxicity data from immunotherapy plus chemoradiation combinations in other solid tumors have been reassuring, as described in the discussion section. The first three (3) patients with locally advanced or unresectable disease will receive cycle 1 of pembrolizumab followed by a break and resumption of pembrolizumab at cycle 4 and as part of a safety cohort. These patients will receive a total of 10 cycles of pembrolizumab (Fig. 1). All other patients, including the fourth patient with locally advanced/unresectable disease, will receive weekly cisplatin and pembrolizumab every 3 weeks, concurrently with daily radiation therapy (Fig. 2). Following completion of Cis-RT, patients will continue pembrolizumab maintenance for a total of 10 cycles in the safety cohort or 12 cycles for all other participants. Archived tissue will be used for MSI, PD-L1 and TIL stratification post hoc. Imaging will be performed at baseline and every 3 cycles (21-day cycles) as per standard-of-care. Laboratory analysis will occur on the first day of each cycle. We will collect and evaluate HPV status, PD-L1, and MSI status prior to therapy, but this will not be used for eligibility. Radiographic imaging will be performed every 9 weeks and overall response rate will be determined by RECIST 1.1 criteria.

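### Rejecting a single 30% null in a mixed population can show activity, but not that pembrolizumab raises response over cisplatin-radiation, least of all in locally advanced disease

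*Protocol article*

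**What the plan says.** All places are in the Protocol article.

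- **Hypothesis** (Aim and study design): "Addition of pembrolizumab to cisplatin-sensitized radiation (Cis-RT) therapy is hypothesized to increase overall response rate".
- **Endpoint and size** (Statistical considerations): "The primary endpoint for this study is overall response rate (ORR"), and "The target enrolment is 24 patients".
- **Test** (same section): "the power to reject Ho: ORR ≤ 30% in favor of H1: ORR ≥ 60% will be 89" per cent, "at a target significance level of 0.05 for a one-sided exact Binomial test". Twelve or more responses count as success.
- **Benchmarks** (same section): "an ORR of 40% in patients with advanced or recurrent metastatic vulvar cancer treated with platinum-based combination therapy"; about 12% for single-agent chemotherapy; and "Patients with primary disease who are not candidates for upfront surgery have a reported response rates from 55% [30] to 64% [11"].
- **Source of the 64%** (Background): it comes from a study of cisplatin-sensitised radiation in locally advanced disease. "They reported a 64% response rate, allowing for many of these patients to subsequently undergo consolidative surgery". The treatment behind the 55% is not named.
- **Population** (Patient characteristics and Table 1): the trial takes unresectable, incompletely resected, recurrent and metastatic cases. Patients may be untreated, or pretreated with up to two cytotoxic lines if recurrent. No expected proportions are given, and one null applies to everyone.

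**The concern.** The hypothesis compares the triplet with cisplatin-radiation, but the test compares it with a fixed 30%. For locally advanced patients the article's own rate for cisplatin-radiation without pembrolizumab is 64%, more than twice the null. The success threshold of 12/24 is 50%, which is below both ends of the 55–64% range, and the 60% alternative lies within that range. A locally advanced cohort could reach the design target and show no gain.

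The null is also not tied to who enrols. The benchmarks run from 12% to 64% by treatment and disease group, so the response rate expected without any pembrolizumab effect moves with the case mix while the cutoff stays at 12. At stake is what a positive trial would mean: the nominal 5% error protects against a response rate of 30% or less, not against pembrolizumab adding nothing.

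**Working it through.** **Inputs.** From Statistical considerations: n = 24, cutoff 12, null 30%, alternative 60%, one-sided 0.05, and benchmarks of 12%, 40%, 55% and 64%. Numbers of patients per disease group are my assumptions, because the article gives none.

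**Step 1: reproduce the design.** P(X ≥ 12) = Σ C(24,x) p^x (1−p)^(24−x), summed over x = 12 to 24.
- p = 0.30: 0.0314. A cutoff of 11 would give 0.0742, so 12 is the correct cutoff.
- p = 0.60: 0.8857, which matches the stated 89%.

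**Step 2: the same rule if every patient responded at one benchmark rate.**
- p = 0.40: 0.213
- p = 0.55: 0.758
- p = 0.64: 0.947

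The last two describe an all-primary cohort and are limiting cases.

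**Step 3: mixed cohorts.** Let X = A + B, with A ~ Bin(m, p₁) for m primary patients and B ~ Bin(24−m, p₂) for the rest. P(X ≥ 12) comes from the convolution. Each cell gives the average rate, then P(X ≥ 12).

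| Primary of 24 | Rate in the rest | Primary at 55% | Primary at 64% |
|---|---|---|---|
| 8 | 12% | 26.3%; 0.5% | 29.3%; 1.0% |
| 12 | 12% | 33.5%; 4.7% | 38.0%; 11.6% |
| 16 | 12% | 40.7%; 21.3% | 46.7%; 44.7% |
| 8 | 40% | 45.0%; 38.4% | 48.0%; 50.2% |
| 12 | 40% | 47.5%; 48.2% | 52.0%; 66.1% |
| 16 | 40% | 50.0%; 58.2% | 56.0%; 79.5% |

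**Step 4: can 30% arise as a blend?** Not from 40% and 55–64%, since any such blend is at least 40%. With 12% for the rest, the primary share must be (0.30 − 0.12)/(0.64 − 0.12) = 0.35 or (0.30 − 0.12)/(0.55 − 0.12) = 0.42. So 30% is reachable with about 35–42% primary disease, but the article states no such derivation.

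**Step 5: what a higher null would cost at n = 24.** Smallest cutoff with size at most 0.05:
- Null 40%: ≥ 15 responses, size 2.2%, power 49% at 60% and 85% at 70%.
- Null 45%: ≥ 16, size 2.7%, power 33% at 60% and 73% at 70%.
- Null 50%: ≥ 17, size 3.2%, power 19% at 60% and 56% at 70%.

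Testing 40% against 60% at about 89% power would need about 55 patients (≥ 29 responses).

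**The case against.** A reader might infer that the trial's true error rate is 76–95%, or at least 21%. The documents do not support a fixed figure.

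- The 76% and 95% need a cohort made up wholly of primary disease, which the article does not describe.
- The 40% belongs to platinum combination chemotherapy, not to this trial's backbone of single-agent cisplatin with site-directed radiation. The Background reports no responses to cisplatin alone, Study procedures excludes thoracic metastases from irradiation, and recurrent patients may have had two cytotoxic lines. No rate for cisplatin-radiation in metastatic disease is given.
- The 12% is no better matched: the Background ties it to single-agent paclitaxel. With that rate and 8 of 24 primary, the rule is conservative (0.5–1.0%).

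A reader might also take the whole 55–64% range as chemoradiation without pembrolizumab. Only the 64% is identified as such. Nor does the article say that these historical rates used RECIST 1.1, as this trial does.

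Finally, the source of the 30% and a breakdown by disease group may stand in the full protocol or analysis plan, so their absence from an article carries little weight.

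All of this stands, and it limits the size of the claim. It does not remove the mismatch between the hypothesis and the test. The article itself fixes the null, alternative and cutoff, and they sit beside a 64% rate for the same backbone. That a single arm is usual in a rare disease is accepted; the design is not the complaint.

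**Conclusion.** The point holds in this form: one unweighted 30% null for a mixed population cannot support the claim that pembrolizumab raises response over cisplatin-radiation. It fails most clearly in locally advanced disease, where the target itself is within the range already reported. The size and power calculations are correct.

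The probability of success with no added benefit is not one number. Across the mixed scenarios above it runs from 0.5% (8 primary, others at 12%) to 79.5% (16 primary at 64%, others at 40%). That spread rests on assumed case mixes and on borrowed rates for recurrent and metastatic patients, and it is itself the reason to tie the null to case mix. Severity: should fix.

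**What to change.** Keep 24 patients and amend the statistical section.

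1. State that rejecting a response rate of 30% or less shows activity of the combination and does not show benefit over cisplatin-radiation.
2. Report response with an exact confidence interval separately for locally advanced or unresectable patients and for recurrent or metastatic patients. Set the locally advanced result against the 55–64% range, and say in advance which group incompletely resected patients join.
3. Either show the expected case mix and group rates from which 30% follows, or replace it with a case-mix-weighted null fixed before analysis and restate cutoff and power. A null of 40%, for example, needs 15 or more responses (size 2.2%, power 49% at 60%, 85% at 70%).
4. In either case, give the false-success probability of the 12/24 rule at the protocol's own benchmark rates, showing 12% and 40% side by side for recurrent or metastatic patients.

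**Cost.** Items 1, 2 and 4 need only text and a short calculation, at the price of a narrower conclusion. Raising the null under item 3 needs no extra patients but lowers the stated power: 49% at the current 60% alternative for a 40% null, and less for higher nulls. The documents offer no support for a 70% alternative, so a sponsor choosing that route would have to justify it.

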### Analysis strategy

Exact Binomial test and 95% CI for ORR (primary endpoint). For the secondary objectives of RFS-6, a point estimate with exact 95% CI and Kaplan–Meier estimate will be used for the RFS distribution. Operating characteristics of prediction (sensitivity, specificity, positive- and negative predictive values with 95% CI) for the baseline dMMR/MSI-status and PD-L1, and descriptive analysis will be used for anti-tumor inflammatory cytokines and HMGB-1 levels.

## Discussion

There are numerous clinical trials that support safety of the combination of chemotherapy with immune checkpoint blockade [31–33]. In addition, there is prospective safety data for combining chemoradiation with immune checkpoint blockade. Phase 2 and 3 clinical trials in NSCLC evaluating concurrent platinum-based chemotherapy with RT and PD-L1 blockade reported an incidence of about 30% in adverse related events [27, 34]. This is not significantly higher than what would be expected for chemoradiation treatment alone. A phase 1 trial by Tang et al. evaluated the combination of hypofractionated radiotherapy; 50 Gy in 4 fractions or 60 Gy in 10 fractions, with ipilimumab in patients with metastatic solid tumor malignancies [35]. In this study, 34% of patients developed grade 3 toxicity with colitis being the most common adverse event. Of note, 23% of the patients treated on this trial derived benefit via abscopal effects [35]. Another phase I trial combined pembrolizumab with various courses of radiation therapy; 30 Gy in 3 fractions for osseous metastasis, 50 Gy in 5 fractions for central lung tumors and 45 Gy in 3 fractions for other sites [36]. Only 6% of the 62 participants in this trial experienced grade 3 toxicities. The authors also reported abscopal effects in 13.2% of these patients [36]. NRG-GY017 is an ongoing phase I clinical trial evaluating an anti-PD-L1 inhibitor, atezolizumab, in patients with node positive Stage IB2, II, IIIB, or IVA cervical cancer. Similar to this trial, both arms of the study include the administration of immune checkpoint blockade concurrently with cisplatin-sensitized radiation therapy at doses similarly used for GYN malignancies, and there have been no adverse safety signals reported (NCT 03738228). As a safety precaution, the first three patients with locally advanced unresectable disease treated on this trial with receive pembrolizumab on cycle 1 and then resume on cycle 4 and on (Fig. 1).

Several preclinical studies show that combination cisplatin and radiation therapy increases the immunogenetic effect of each treatment modality in ways that can be further enhanced by PD-1/PD-L1 blockade. By adding pembrolizumab early during the delivery of Cis-RT, the opportunity for antigen capture and presentation, DC priming and T-cell activation is potentially increased. The pragmatic design of this trial also allows for collection of translational correlatives to evaluate if a systemic anti-tumor inflammatory response is being generated by this triplet combination.

In a rare disease with limited options in the recurrent setting, addition of immune checkpoint blockade to cisplatin-sensitized radiation could provide durable disease control by engaging the immune system.

## Data Availability

At the completion of the trial, de-identified data will be available upon request.

## Abbreviations

PD-L1: Programmed death receptor 1-ligand
PD-L2: Programmed death receptor 2-ligand
HPV: Human papillomavirus
TIL: Tumor infiltrating Lymphocytes
MSI: Microsatellite instability
dMMR: Deficient mismatch repair
IL-2: Interleukin 2
DC: Dendritic cell
M6P: Mannose-6-phosphate
RT: Radiation therapy
PFS: Progression-free survival
PI: Principal investigator
AE: Adverse event
OS: Overall survival
NSCLC: Non small cell lung cancer
IFN-γ: Interferon gamma
HMGB-1: High-mobility protein box-1
MHC: Major histocompatibility complex
AE: Adverse events
GTV: Gross tumor volume
CTV: Clinical tumor volume
PTV: Planning tumor volume
OAR: Organs at risk
CTCAE: Common terminology criteria for adverse events
IHC: Immunohistochemistry
ELISA: Enzyme-linked immunosorbent assay
ORR: Overall response rate
RFS: Relapse free survival
